**Discussion:**

Results from the posttreatment measurement can be considered strong empirical indicators of the effectiveness of VRETp. The 6-month follow-up data may provide reliable documentation of the long-term effects of the treatment on the outcome variables. Data from pre-treatment and mid-treatment can be used to reveal possible pathways of change.

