## Background

A large number of patients with a psychotic disorder participate poorly in society, even if their psychotic symptoms have been treated successfully. Unemployment is high at 80–85 % [1] and about 75 % do not have a relationship with a partner [2]. A study comparing the social network of young people with early psychosis and matched controls showed that the psychosis group had smaller networks, fewer friends, fewer people to turn to in a crisis, and a greater likelihood of service providers as members [3]. Social network size is also associated with the likelihood of in-patient treatment and with the number of services used by psychotic patients [4]. Social isolation hinders patients in multiple areas of functioning, such as developing and maintaining a social network, the ability to function in work-related environments, and even in performing daily tasks needed for independent living (e.g., shopping for groceries). When psychotic disorders are in partial remission, the remaining feelings of paranoia and delusions of reference often cause patients to avoid places and people. Moreover, this conditioned avoidance does not improve with antipsychotic medication [5].

**Table 1 Tab1:** Measurement objectives

Outcome	Measurement	T0	T1	T2	T3	T6
	Interview (i) Self-report (s)	Baseline	Session 4	Session 8	Posttreatment	Follow-up
Social participation	Experience Sampling Method (s)	x			x	x
Paranoia	GPTS (s)	x	x	x	x	x
Interaction anxiety	SIAS (s)	x	x	x	x	x
Depression	BDI-II (s)	x			x	x
Stigma	ISMI (s)	x			x	x
Schemas	BCSS (s)	x			x	x
Safety behavior	SBQ (i)	x			x	x
Cognitive biases	DACOBS (s)	x			x	x
Social functioning	SOFAS (i)	x			x	x
Quality of life	MANSA (i)	x			x	x
Cost-effectiveness	TIC-P (i)	x			x	x
Cyber sickness	SSQ (s)		x	x		
Presence	IPQ (s)		x	x		
Medication adherence	BARS (i)	x	x	x	x	x

*GPTS* Green et al. Paranoid Thought Scales, *SIAS* Social Interaction Anxiety Scale, *BDI-II* Beck Depression Inventory, *ISMI* Internalized Stigma of Mental Illness, *BCSS* Brief Core Schema Scales, *SBQ* Safety Behavior Questionnaire – persecutory delusions, *DACOBS* Davos Assessment of Cognitive Biases Scale, *SOFAS* Social and Occupational Functioning Assessment Scale, *MANSA* Manchester Short Assessment of quality of life, *TiC-P* Trimbos/iMTA questionnaire for Costs associated with Psychiatric illness, *SSQ* Simulator Sickness Questionnaire, *IPQ* Igroup Presence Questionnaire, *BARS* Brief Adherence Rating Scale

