## Design

The study is a single blind randomized controlled trial (RCT) with two conditions: (i) the active condition in which subjects receive the VR treatment besides treatments as usual (TAU) and (ii) the waiting list condition during which subjects receive TAU only. All participants on the waiting list are also offered the VR treatment after follow-up measurements have been completed. The two groups are compared at baseline, at 3 months posttreatment and at 6 months follow-up. The waiting list condition receives the VRET treatment after 6 months.

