### Procedure

Patients with a chart diagnosis of schizophrenia, schizophreniform disorder, schizoaffective disorder, delusional disorder or psychotic disorder not otherwise specified (NOS), will be informed about the study by their treating specialist and asked to participate. Each patient is asked for written permission to be contacted by the researchers if eligible for VRETp. If eligible, the treating specialist discusses participation of the patient in the study with the remainder of the team and gives permission to the researchers to contact the patient. When permission is given, additional information is provided and patients have 2 weeks to consider whether they really wish to participate. The VRETp treatment is additional to current treatment and declining to participate has no negative consequences at all for patients. For each of the participating organizations an independent specialist is available for patients to contact. Contact information of this specialist is available in the information letter given to the patients of the participating organizations.

Informed consent from all participants is obtained before assessment by the researcher. The MINI-Plus interview is used to diagnose psychotic disorders. Patients who are willing to participate are screened for avoidance behavior (SBQ) and for paranoia using the GPTS (cutoff >40) of Green et al. Baseline measurements are obtained. Randomization is used to allocate a patient to either the VRETP or to the waiting list condition. Patients allocated to the VRETp group start their treatment, which consists of a maximum of 16 sessions with a maximum duration of 60 minutes each.

At baseline (T0) the research assistant assesses the baseline measurement of all primary and secondary variables. At 2 weeks (T1) and 4 weeks (T2) into treatment, respectively, participants in the treatment condition are assessed for their scores on paranoia, interaction anxiety, cyber sickness, presence in the virtual world and medication adherence, using self-report questionnaires handed out by the therapist, or interview questions (medication adherence).

At the end of treatment (T3) and at follow-up (T6), the research assistant assesses the primary and secondary measures.

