### Virtual reality exposure therapy (VRET)

VRETp treatment has a maximum of 16 treatment sessions of 60 minutes each. This number of sessions is somewhat larger than is usual for CBT in anxiety disorders. Our rationale for this is our expectation that treating paranoia requires more time compared with treating regular anxiety. People suffering from a psychotic disorder often show severity and durance in their social avoidance. Negative symptoms make it difficult to motivate people for therapy and this is a continuing process during treatment. The treatment protocol states that the therapists receive 16 hours of training; all therapy sessions are recorded. A selection of the sessions is rated for treatment fidelity using the Cognitive Therapy Rating Scale (CTRS). The CTRS is a reliable [41] and valid [42] instrument to measure treatment fidelity when following a CBT protocol. Monthly 4-hour group supervision serves to guide the therapists throughout the intervention period.

Existing CBT protocols will be adapted for VRET treatment in one area: exposure in vivo will be replaced by VR exposure. The remainder of the treatment protocol consists of well-known, evidence-based CBT elements, e.g., providing treatment rationale, behavioral experiments, reducing safety behavior, and attention training. Starting with exposure exercises for social situations, which are lowest in the patient’s anxiety hierarchy, the exposure exercises take place during the therapy session using the Virtual Reality system. Participants are not allowed to receive any other form of therapy aimed at improving social participation during the trial. At all times the therapist is in control of the VRETp intervention and is able to immediately change/stop the virtual environment if necessary.

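### T3, the first post-baseline assessment of the primary outcome, is tied both to month 3 and to the end of treatment; the second anchor does not exist for the waiting list and can vary with response

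*Protocol article*

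**What the plan says.** The protocol article describes the timing of T3 in three places.

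- **Design** (and, in the same terms, the Abstract): "The two groups are compared at baseline, at 3 months posttreatment and at 6 months follow-up". This gives nominal times common to both arms.
- **Procedure**: "At the end of treatment (T3) and at follow-up (T6), the research assistant assesses the primary and secondary measures". This is an event, with no calendar time attached.
- **Table 1**: the T3 column is headed "Posttreatment", and the experience sampling measure, which carries the primary outcome, is scheduled at T0, T3 and T6 only.

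Four other statements bear on how these fit together.

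- Table 1 puts T1 at session 4 and T2 at session 8. The Procedure section gives the same two points by calendar: "At 2 weeks (T1) and 4 weeks (T2) into treatment, respectively, participants in the treatment condition are assessed".
- The VRET section sets the length of a course: "VRETp treatment has a maximum of 16 treatment sessions of 60 minutes each".
- The Early completions section lets treatment end sooner, once distress has been zero in every relevant virtual situation for two sessions in a row.
- The Design section says of the controls: "The waiting list condition receives the VRET treatment after 6 months". It also says that this offer follows completion of their follow-up measurements.

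The Abstract's discussion says of the last time point: "The 6-month follow-up data may provide reliable documentation of the long-term effects of the treatment on the outcome variables".

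**The concern.** A calendar anchor and an event anchor give the same assessment date only if every course of treatment ends at about month 3. The protocol's own session timing does not show that it does, and the early-completion rule makes the end of treatment differ between patients.

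The event anchor also has no counterpart in the control arm. A waiting-list participant has no end of treatment before T3, and the Procedure section does not say what takes its place. If a site schedules T3 from that section, VRETp patients are assessed after their own last session and controls at some other time. Two things follow.

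- Time since randomisation can differ between the arms in the primary comparison.
- For early completers, the assessment date is set partly by their own response, because treatment stops when in-session distress has reached zero. Their primary outcome would then be read at a moment chosen because they were doing well.

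An analysis that treats T3 as one nominal visit would not remove either effect.

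**Working it through.** **1. Pace implied by the protocol.**
Inputs: session 4 and session 8 (Table 1); 2 and 4 weeks into treatment (Procedure).
4 / 2 = 2 sessions per week; 8 / 4 = 2 sessions per week. The two descriptions of T1 and T2 agree with each other.

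**2. Calendar anchor in weeks.**
One month = 365.25 / 12 / 7 = 4.348 weeks. Month 3 = 13.0 weeks; month 6 = 26.1 weeks.

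**3. End of treatment against month 3**, counting from the start of treatment:

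| Case | End of treatment | Gap to month 3 |
|---|---|---|
| 16 sessions, two a week throughout | 16 / 2 = week 8 | 13.0 − 8 = 5.0 weeks |
| 16 sessions, weekly after session 8 (assumed) | 4 + 8 = week 12 | 13.0 − 12 = 1.0 week |
| Early completion at session 12, two a week (illustration) | 12 / 2 = week 6 | 13.0 − 6 = 7.0 weeks |

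The protocol gives no pace after session 8, so the first two rows show how much the answer depends on it.

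**4. Reverse check.** An even pace that fills 13.0 weeks is 16 / 13.0 = 1.23 sessions per week. Session 4 would then fall at 4 / 1.23 = week 3.3 and session 8 at 8 / 1.23 = week 6.5, against the stated weeks 2 and 4. An even pace therefore cannot satisfy both the stated session timing and a full course ending at month 3.

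**5. Start of treatment.** The 2 and 4 weeks count from the start of treatment, and the article gives no interval from randomisation to the first session. Any delay moves the end of treatment later by the same amount. A delay of about 5 weeks would close the gap in the first row, but not for early completers.

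**6. Distance to T6.** The controls' treatment follows their follow-up measurements and comes after 6 months, so T6 most naturally lies at month 6 from baseline.
- From a month-3 T3: 6 − 3 = 3 months.
- From a week-8 end of treatment: 26.1 − 8 = 18.1 weeks, and 18.1 / 4.348 = 4.2 months.
- From a week-12 end of treatment: 26.1 − 12 = 14.1 weeks, or 3.2 months.

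**7. Another reading of the Design sentence.** If it meant 3 months after treatment has ended, T3 would fall at 8 + 13.0 = week 21. That contradicts the Procedure section outright, so month 3 from baseline is the more natural reading.

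**The case against.** The strongest reply is that the Design section already states common times for both groups, and that the labels T3 and T6 themselves suggest months 3 and 6. On that reading the end of treatment in the Procedure section is loose wording for month 3. Nothing there says that the assessment moves with each patient's last session, and the early-completion rule moves no assessment. The 5-week gap also needs the pace to continue past session 8, which the article does not state. Assessment windows may be set out in a full protocol that is not shown, and the flow diagram is missing.

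Much of this stands. The absence of windows is not a finding, and the size of the gap is conditional. What remains is that two sections of one document define the primary assessment differently, and one definition cannot be applied to half of the participants.

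A reader might go further in four ways that the document does not support.

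- **That the session pace fits neither anchor.** The end of treatment is an event with no stated week, so a week-8 finish is compatible with it. The pace is in tension only with month 3.
- **That treatment may run to week 16 on weekly sessions.** This contradicts the stated timing of sessions 4 and 8.
- **That T1 and T2 are contradictory.** Their session and week definitions agree (step 1).
- **That controls may cross over before T6.** The Design section and the Abstract both place their treatment after the follow-up measurements.

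**Conclusion.** The point holds as an inconsistency in the definition of T3. A reader might infer that the protocol prescribes assessment of the two arms at different times. It does not: under the Design section's common times the arms are aligned. Unequal and partly response-dependent timing is a risk that arises if the Procedure section is followed literally.

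For a full course the two anchors differ by about 5 weeks if two sessions a week continue to session 16, and by about 1 week if sessions become weekly after session 8. The gap is larger for early completers. These figures assume that treatment starts soon after randomisation and that month 3 is counted from baseline.

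A secondary point concerns the follow-up claim. If T6 is at month 6 from baseline, it lies about 3 months after a month-3 T3, or about 4 months after a week-8 end of treatment. Calling this long-term is generous. The reason is that the 6 months are counted from baseline; a faster session pace lengthens the interval after treatment.

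The sample size of 160 is unaffected. The matter should be corrected because it concerns the timing of the primary outcome and the remedy is nearly free.

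**What to change.** 1. In the Procedure section and Table 1, define T3 and T6 from randomisation, at month 3 and month 6, in both arms and with the same window, regardless of the number of sessions attended or early completion.
2. Have the sponsor reconcile the session pace implied by T1 and T2 with the label that equates posttreatment with 3 months. How many sessions are given, and how often, is for the sponsor to settle; the assessment date should not depend on it.
3. In the Abstract's discussion, replace the long-term description of the 6-month data with the actual interval: about 3 months after T3.

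The cost is a change of wording and of assessor scheduling. It adds no visits and leaves the sample size as it is. The article gives the trial as ongoing, so assessments still to come can be aligned. For those already made, a table of time from randomisation to T3 by arm would show whether the risk materialised.

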### Randomization

A block of 12 random assignments will be made for each participating mental health center. Each block has six assignments for each condition: VRETp or waiting list. If a center includes more patients, new blocks of 12 random assignments will be made available. The blocks are made using a scientific randomization program (www.randomizer.org) by the independent randomization bureau of Parnassia Psychiatric Institute. Participants and therapists are informed about the randomization by mail and email, respectively.

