### Unblinding

The study is single-blinded, meaning that research assistants who do the measurements are kept blinded regarding randomization of the participants. Participants are regularly instructed not to tell the research assistants which group they are allocated to; if a research assistant is accidentally unblinded during a measurement, that measurement is stopped. A new appointment is then made with another blinded research assistant.

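### Fixed blocks of 12 within each centre let staff who know earlier allocations be certain of the last assignment(s) in any completed block; undisclosed random block sizes would remove nearly all of that certainty

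*Protocol article*

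**What the plan says.** The Randomization section of the protocol article fixes size, ratio and stratum. It states "A block of 12 random assignments will be made for each participating mental health center", then "Each block has six assignments for each condition: VRETp or waiting list", and for continued recruitment "If a center includes more patients, new blocks of 12 random assignments will be made available". It describes no variation in size. The lists are made "by the independent randomization bureau of Parnassia Psychiatric Institute".

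On who learns the result, the same section says "Participants and therapists are informed about the randomization by mail and email, respectively". The Unblinding section limits blinding to assessors: "research assistants who do the measurements are kept blinded regarding randomization of the participants". On who is put forward, the Procedure section says that "the treating specialist discusses participation of the patient in the study with the remainder of the team and gives permission to the researchers" to make contact. A two-week reflection period, consent, diagnostic and symptom screening, and baseline measurement follow before the patient is randomized. Trial status at publication is given as ongoing.

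**The concern.** With a constant block size, the running count of allocations at a centre reveals what is left in the block. Once six patients have gone to one arm, every remaining place belongs to the other. An independent bureau keeps the list itself safe, but it does not stop anyone from counting past allocations. Here the count is visible to some people at the centre, because therapists are told the allocations, and the size is in print.

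If those who put patients forward have that knowledge, they can hold back or bring forward a patient according to the arm that comes next. The arms may then differ at entry. Intention-to-treat analysis and blinded assessors do not correct a difference created before randomization. The primary outcome is self-assessed by participants who know their arm. The section on the VR therapy describes motivation as a continuing difficulty in this population, so there is a plausible characteristic on which patients could be selected.

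**Working it through.** **Inputs from the protocol article.** Block of 12, split 6:6, within centre (Randomization); seven centres (Participants); 160 patients (Power and sample size calculation). **Assumption:** equal centres, 160/7 = 22.9, so about 23 patients each. The article states no figure for predictability, so there is none to reproduce.

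**Step 1. Certain assignments in a complete block.** The certain assignments are the final run of identical ones. For a block of 2m = 12,

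P(final run is exactly k) = 2 × C(11 − k, 6 − k) / C(12, 6), with C(12, 6) = 924.

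- k = 1: 2 × C(10, 5)/924 = 504/924 = 0.545
- k = 2: 2 × C(9, 4)/924 = 252/924 = 0.273
- So the last assignment is always certain, at least the last two in 1 − 0.545 = 45.5% of blocks, and at least the last three in 45.5% − 27.3% = 18.2%.
- Expected number over k = 1 to 6: 12/7 = 1.71 of 12, or 14.3%.

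**Step 2. Certain assignments at 23 patients per centre.** The first block completes and the second stops at its 11th place, so its always-certain 12th place is never used.

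- Per centre: 12/7 + (12/7 − 1) = 17/7 = 2.43 of 23, or 10.6%.
- Whole trial: 0.106 × 160 = about 17. A simulation with six centres of 23 and one of 22 gives a mean of 16.6 (95% range 10 to 24).

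**Step 3. Guessing from the running balance** (always guess the arm that is behind; a tie counts one half).

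- Complete block: 6 + (2^12/924 − 1)/2 = 6 + (4.433 − 1)/2 = 7.72 of 12, or 64.3%.
- 23 patients: (7.72 + 6.72)/23 = 14.43/23 = 62.8%. The missing 12th place would always have been guessed correctly, hence 6.72 for the second block.

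**Step 4. The same quantities with random sizes.** Sizes are drawn with equal chance from 8, 10, 12, 14 and 16, with 23 patients per centre. The simulated observer knows the set of sizes but not the order drawn, and updates after each allocation.

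| Scheme, 23 per centre | Certain | Of 160 | Best guess correct |
|---|---|---|---|
| Fixed 12 | 10.6% | about 17 | 62.8% |
| Random 8 to 16 | about 0.5% | under 1 | 62.3% to 62.4% |

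**Step 5. Other fixed sizes, for scale.** The certain share of a complete block is 33% for size 4, 25% for size 6 and 20% for size 8, so 12 is already at the favourable end. Random sizes from 4, 6 and 8 would leave about 4 of 160 certain but raise best-guess accuracy to 67%, so small sizes are not a good replacement.

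**The case against.** Several points on the other side are sound.

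- **Access is inferred.** Therapists are told allocations, whereas the treating specialist and team do the referring. The article does not say that referrers see the centre's complete history, which certainty requires. This stands. What remains is that the two groups work at the same centres and the design does not depend on keeping them apart.
- **Aiming at a slot is hard.** Team discussion, permission, two weeks to consider, consent, screening and baseline come between referral and randomization. Patients may decline or fail screening, and others at the centre may be randomized meanwhile. This stands and lowers the practical risk.
- **Incentive is limited.** Everyone on the waiting list is offered the treatment after follow-up. This also stands.
- **Twelve is a large block, and lists already come from an independent bureau after baseline.** True, but neither prevents counting.

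Stronger readings are tempting but not supported. A reader might call the trial open; the article describes it as single-blind, open only to participants and therapists. A reader might say the end of every block is known; this applies only to completed blocks. A reader might also turn guessing into a bias. With a steer of 0.1 SD towards the guessed arm, 2 × 0.1 × (0.643 − 0.357) = 0.057 SD, or 11% of the planned effect of 0.5. The 0.1 SD has no source in the article, and the figure rests on running-balance guessing, which random sizes hardly change. At 23 patients per centre the same formula gives 2 × 0.1 × (0.628 − 0.372) = 0.051 SD with fixed blocks and 2 × 0.1 × (0.623 − 0.377) = 0.049 SD with random ones. It cannot be presented as the benefit of the change.

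**Conclusion.** The weakness is real and modest. Fixed blocks of 12 within centre make 14% of assignments in a complete block, and about 10.6% of all assignments (about 17 of 160), certain to anyone who knows every earlier allocation at that centre. The whole-trial figure assumes seven equal centres. Its consequence depends on referrers having that knowledge, which the article makes plausible but does not state, and on their being able to time a patient's entry, which the procedure makes difficult. Nothing in the article shows that selection occurred, and no size of bias can be derived from it. The sample size, power and alpha are unaffected. This is a cheap improvement to the design, not an error that invalidates it.

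**What to change.** For any blocks still to be issued, the independent bureau should draw the block size at random within centre, for example from 8, 10, 12, 14 and 16, and keep the sizes undisclosed to centres and researchers. Sizes of 4 to 6 should be avoided. One protocol sentence can record that sizes vary and are withheld, without listing them.

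The cost is one new list per centre and that sentence. The downside is slightly more possible imbalance between arms if a centre closes mid-block. The article says only that the trial is ongoing, so the sponsor must establish whether any blocks remain; if none do, the change no longer applies.
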